#### Measurement Tools

Baseline demographic characteristics will be collected via the participant information questionnaire, which is described in the measurement tools section in the Phase I study. Implementation outcomes will describe the feasibility of using the app with Chinese Canadian seniors in the community. Implementation will be measured as:

Accrual and attrition rates: The mDASHNa-CC recruitment log has been designed to record data related to the number of eligible seniors per recruitment day, reasons for ineligibility, and reasons for nonparticipation. The mDASHNa-CC Activity Log has been designed to record data on attrition, including occurrence/reasons for attrition, technical difficulties, adherence, and outcome measure completion. A trained research assistant will complete the logs daily during the research process.Technical issues: The occurrence and description of technical problems will be recorded on the mDASHNa-CC activity log by a trained research assistant.Acceptability: The acceptability e-scale ascertains perceptions related to how helpful, difficult, and enjoyable electronic-based programs are to use, how understandable questions are, and how acceptable the time invested in reporting was [65]. This scale demonstrated validity and reliability in various prior studies [65]. For the present study, the wording of the scale will be slightly modified, and a free-text question, where seniors are encouraged to enter any other information that they feel would be important to discuss, will be added. Seniors in the intervention group will fill out this scale by email four weeks and eight weeks postrandomization.Adherence: A built-in number counter will measure participants’ adherence to the requirements of learning dietary educational material, conducting dietary self-assessments, and monitoring blood pressure in the mDASHNa-CC app. The number counter will record the time and frequency of app use. The dietary intake will be measured at baseline and eight weeks postrandomization by a one-to-one dietary interview using the validated Automated Multiple Pass Method [66] by a trained research assistant in the community center. This approach was successfully tested in the DASHNa-CC pilot trial. Adherence to the DASH will be measured by the validated DASH component score of each food group, and the total DASH score [67]. Adherence to the sodium reduction will be measured by a 24-hour urine test [68]. Adherence to TCM food therapy will be measured using a 24-statement questionnaire on a 5-point Likert scale, which was validated in the DASHNa-CC pilot study [69].

#### Preliminary Effectiveness and Outcomes

Except for health service utilization, which will be measured only at eight weeks postrandomization, the other following outcomes will be measured at baseline and eight weeks postrandomization at the community center by a trained research assistant during a one-to-one appointment. If a participant cannot visit the center, a home visit by a trained research assistant will be arranged.

Systolic and diastolic blood pressures: Systolic and diastolic blood pressures will be measured with the home blood pressure monitor, Omron BP785, whose validity and reliability have been tested [70]. All blood pressure measurements will be performed following the recommended techniques by the Canadian Hypertension Education Program guidelines [5]. Each participant will be offered an Omron BP785 and training on how to measure blood pressure at home and how to record the results; however, blood pressure at baseline and eight weeks postrandomization will be measured by a trained research assistant.Bodyweight: An electronic body weight scale will measure weight.Waist circumference: Waist circumference will be measured by measurement tape following proper techniques [71-74].Health-related quality of life: Health-related quality of life will be measured by the SF-36v2 [75,76].Health service utilization: Health service utilization data will be collected via the Health Service Utilization Questionnaire, which was modified from the Health Service Utilization Questionnaire previously used in Ontario [77].

### Data Analysis and Statistical Methods

Demographic data will be analyzed using the software SPSS version 20.0 by a biostatistician. To describe the sample, various descriptive statistics (eg, means, standard deviations, proportions), dependent on the level of measurement of the variables, will be calculated for sample demographics and other baseline information. Descriptive statistics will be calculated to demonstrate how participants adhered to and are satisfied with the app. Open-ended questions will be reviewed by two researchers independently. Qualitative data will be organized into meaningful groups, combining similar patterns into themes. In feasibility testing, adherence is defined as 100% when 28/28 blood pressure entries and 14/14 dietary self-assessments entries are completed within the two weeks. An independent, two-sample, two-tailed *t* test will be used to examine the differences in mean change scores between the control and intervention groups regarding blood pressure, weight, waist circumference, and health-related quality of life.

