#### App Design

Based on the findings of the DASHNa-CC pilot trial, the major functions of the app will include: (1) antihypertensive dietary education; (2) dietary self-assessments; (3) automatic feedback according to dietary self-assessments; (4) blood pressure monitoring; and (5) automatic feedback according to blood pressure data. To enhance individuals’ interest in using the app, a new function of the app that will be utilized is built-in age and culture-specific entertainment content as a reward for learning dietary education material, conducting dietary self-assessment, and monitoring blood pressure [57]. The entertainment content, including Chinese songs, videos, or Beijing opera, will be suggested by senior Chinese Canadians in the community.

The antihypertensive dietary education is based on the DASHNa-CC intervention and includes the content of the DASH diet pattern, sodium reduction, and TCM food therapy. It is recommended that participants review the educational content and answer the related questions, and they will also be asked to conduct a dietary self-assessment every day on the app. Based on this, the app will automatically provide feedback and suggestions. Participants are also asked to measure their blood pressure twice a day using a home blood pressure monitor. They will then record the data in the app, which will automatically provide feedback regarding their blood pressure status. Frequent use of the app will be rewarded with built-in entertainment content. The data entered by seniors will be stored locally on the smartphone and then communicated to the server when the phone is online using an encrypted protocol. The server will be hosted at Nipissing University behind a firewall in a secure network environment. A username and password will be required to access the data. The app development will be completed by a software programmer who has extensive experience in educational smartphone app development in the Chinese Canadian community.

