### Phase II: Feasibility Testing of mDASHNa-CC App

Following usability testing, a pilot randomized controlled trial [61] feasibility study will be conducted with Chinese Canadian seniors to determine implementation (primary outcomes, including accrual and attrition rates, technical issues, acceptability of the app, and adherence to the intervention,) and preliminary effectiveness (secondary outcomes, including systolic and diastolic blood pressure, weight, waist circumference, health-related quality of life, and health service utilization). This study is designed as a pilot two-group (1:1) randomized controlled trial with a sample size of 60 participants (block of 20) in a Chinese Canadian community in the Greater Toronto Area.

The sampling procedures and setting will be the same as the Phase I study. A convenience sample of 60 Chinese Canadian seniors will participate in this study. Self-identified Chinese Canadians were recruited if they met the following inclusion criteria: (1) at least 65 years of age; (2) had a systolic blood pressure between 140 to 159 mmHg or a diastolic blood pressure between 90 to 99 mmHg; (3) were able to understand and speak Mandarin and read and write Chinese; and (4) had access to a smartphone. Individuals were excluded if they: (1) used antihypertensive medications, insulin, or oral hypoglycemic agents; (2) had a cardiovascular event during the previous three months; (3) had a history of congestive heart failure; (4) had a cancer diagnosis or had undergone cancer treatment during the past two years; or (5) had special dietary requirements.

As a pilot study is not powered to be a hypothesis-testing trial, formal sample size calculations are not recommended [62]. Instead, the sample size suggested was based on recommendations for feasibility trials [63]. In this pilot study, 60 eligible participants will be recruited. Following university ethics approval, participants will be recruited by blood pressure screening events in diverse community settings. The recruitment process of Phase II is the same as that of Phase I. Study procedures will commence after eligibility is assessed, informed consent is obtained, and demographic and baseline outcome data are collected by a trained research assistant.

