Using an online randomization tool provided by Interrand Company, Ottawa, Canada, participants will be randomized into either an intervention group or a control group. Participants randomized to the intervention group will receive the mDASHNa-CC app intervention for eight weeks plus usual care; participants randomized to the control group will receive usual care. Coinvestigators, collaborators, and outcome assessors will be blinded to the group assignment. Because this study is an app educational intervention, it will be impossible to blind participants to the group assignment. The group assignment will be concealed until all outcome data are collected [64]. After all outcome data are collected eight weeks post-randomization, participants in the control group will also be offered use of the app.

The control group will be usual care. Usual care consists of three parts: (1) receiving a general hypertension health education booklet from the Heart and Stroke Foundation of Ontario; (2) being encouraged to see their family physicians or primary health care providers regarding their blood pressure status (those who do not have a primary health care provider will be referred to a walk-in clinic or a community health center); and (3) having access to family physicians, telehealth, emergency care, hospitals, and other health care facilities in the Greater Toronto Area as required.

In addition to usual care, those participants randomized to the intervention group will be offered use of the app. A trained research assistant will teach them how to use it, they will load the app on their smartphones, and then they will be requested to review educational material, conduct dietary self-assessments, and monitor blood pressure for eight weeks. Telephone assistance from a trained research assistant will be available to seniors in case of technical problems or if any questions arise about the app. The research team will conduct a daily review of a summary of each senior’s report so that participant safety issues can be identified and resolved. By the end of the eight weeks postrandomization, seniors will be prompted by phone using an audible alert to complete the app evaluation questionnaire on their smartphone, which will ascertain likes and dislikes with the app.

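### The defined app-adherence percentage, part of a primary outcome, uses an unidentified two-week window holding a quarter of the entries requested over eight weeks, and it leaves out education

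*Protocol article*

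**What the plan says.** The Phase II section of the protocol article lists the implementation outcomes as "primary outcomes, including accrual and attrition rates, technical issues, acceptability of the app, and adherence to the intervention". Participants in the intervention group "will receive the mDASHNa-CC app intervention for eight weeks plus usual care", and "they will be requested to review educational material, conduct dietary self-assessments, and monitor blood pressure for eight weeks".

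The App Design section sets the frequencies. Participants are asked to "measure their blood pressure twice a day using a home blood pressure monitor" and to complete a dietary self-assessment daily. It recommends that they review the education content and answer the related questions, but gives no frequency or number of items.

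Research question 4 asks how far participants adhere to three things: learning the education material, self-assessing diet and monitoring blood pressure. The Phase II Measurement Tools section repeats the three. A built-in counter is to measure "adherence to the requirements of learning dietary educational material, conducting dietary self-assessments, and monitoring blood pressure", and it logs the time and frequency of app use.

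The only numerical rule is in Data Analysis and Statistical Methods, where it is introduced as applying to feasibility testing: "adherence is defined as 100% when 28/28 blood pressure entries and 14/14 dietary self-assessments entries are completed within the two weeks".

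**The concern.** The rule does not fit the design in two respects.

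- **Window.** It refers to a two-week period as if one had been introduced. Phase II has measurements at baseline, four weeks (acceptability scale only) and eight weeks, and no two-week period is defined in either phase. The rule is stated to be for feasibility testing, so it cannot be a leftover Phase I definition.
- **Scope.** It counts two of the three requirements that the article itself names. The Theoretical Framework section treats learning as the foundation of the app, yet a participant who never opens the education material can score 100%.

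At stake is the app-use part of a primary outcome. The Implications section says the pilot is to help launch a full randomised trial, and a reader planning that trial would want to know whether use lasted for eight weeks. As written, the choice of window could be made after the data are seen, and the same records can give very different results.

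**Working it through.** **Inputs**
- Blood pressure entries: 2 per day (App Design).
- Dietary self-assessments: 1 per day (App Design).
- Duration: 8 weeks = 56 days (Phase II).
- Stated denominators: 28 and 14 (Data Analysis and Statistical Methods).

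**Step 1: reproduce the plan's figures.** Entries = rate per day × days in window. For 14 days, 2 × 14 = 28 and 1 × 14 = 14. Both match exactly. So the rule uses the App Design frequencies, and its arithmetic is right for a fortnight.

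**Step 2: entries requested over the whole intervention.** 2 × 56 = 112 blood pressure entries and 1 × 56 = 56 dietary self-assessments.

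**Step 3: coverage of the stated denominators.** 28/112 = 0.25 and 14/56 = 0.25.

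**Step 4: one participant, three windows.** Take someone who makes every entry in weeks 1–2 and none afterwards.

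| Window | Blood pressure | Diet | Score |
|---|---|---|---|
| Weeks 1–2 | 28/28 | 14/14 | 100% |
| Weeks 7–8 | 0/28 | 0/14 | 0% |
| Weeks 1–8 | 28/112 | 14/56 | 25% |

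If the same person instead completes a share q of the entries in weeks 3–8, the eight-week score is (28 + 84q)/112 for blood pressure and (14 + 42q)/56 for diet. Both give 43.75% at q = 0.25, 62.5% at q = 0.50 and 81.25% at q = 0.75. The score for weeks 1–2 is 100% throughout.

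**Step 5: illustration only.** The article gives no rate at which use declines. Assume full use in week 1, each later week at a fraction r of the week before, and a window of weeks 1–2. Mean use over weeks 1–2 is (1 + r)/2; over weeks 1–8 it is (1 − r^8)/[8(1 − r)].

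| r (assumed) | Weeks 1–2 | Weeks 1–8 |
|---|---|---|
| 0.95 | 97.5% | 84.1% |
| 0.90 | 95.0% | 71.2% |
| 0.80 | 90.0% | 52.0% |

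**Step 6: education.** The research question and the counter name three components; the rule scores two. No education denominator can be computed, because the article does not say how many items are assigned.

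**The case against.** The best defence is that the rule uses the right daily rates for two of the three tasks and that eight weeks hold exactly four such fortnights. A score repeated every two weeks is then a natural reading. The reading is possible, but the article does not state it, and it would still leave education out.

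Second, education is measured: the counter covers it, and descriptive statistics on adherence to the app are planned. Since review is only recommended, with no set frequency, leaving it out of an entry-count percentage could be defended. This stands as far as data collection goes. It does not explain why the one defined score covers less than the requirement it is meant to express, and the article gives no reason.

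Third, adherence does not rest on this percentage alone. DASH scores, a 24-hour urine test and a questionnaire on traditional Chinese medicine food therapy measure adherence to the dietary advice. That is correct, but they answer research question 5, not the app-use question.

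Fourth, the outcome is descriptive. No test or sample size depends on it, and the article states no adherence threshold for going on to a full trial. This limits the harm to how a primary outcome is reported and read; a claim that the score decides progression would go beyond the text.

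A reader might also infer that 100% is reached once 28 and 14 entries have accumulated at any time over the eight weeks. The wording rules that out, because the entries must fall within the two weeks.

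**Conclusion.** The concern holds as a conflict between a rule that the article fixes and the article's own design. It is not a detail left for an analysis plan. Two results need no assumption beyond the stated frequencies and duration: the denominators cover 25% of the requested entries, in a window that is not identified; and education, one of three named requirements, is absent from the score. For a participant who uses the app fully for the first two weeks and then stops, the result is 100%, 0% or 25% according to the window.

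Two stronger conclusions are not supported. One is that adherence to the intervention goes unmeasured: the counter records all three tasks, dietary adherence has its own measures, and the score would validly describe blood pressure and diet entries for whichever fortnight it covers. The other is that the reported figure will overstate use by a known amount: that needs a first-two-weeks reading and a rate of decline, and the article gives neither. The decay table only illustrates what could happen under those assumptions.

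**What to change.** Replace the one sentence in Data Analysis and Statistical Methods so that it agrees with research question 4, the Phase II intervention description and the counter:

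1. Score over the full eight weeks: blood pressure entries/112 and dietary self-assessments/56, for all participants randomised to the intervention.
2. Report education completion from the counter as a separate component. The sponsor must state the number of items assigned, since the article does not.
3. If the two-week unit is kept, report all four consecutive windows (28 and 14 each) to show use over time.

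The change concerns scoring only and leaves what participants are asked to do as it is. The cost is one reworded definition plus the education item count; no new data are needed for the entry scores, because the counter already records time and frequency of use. The downside is that the reported adherence figure may be less favourable.

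### The unadjusted t test on change scores is valid, but adjusting for the baseline already collected would give slightly more precise estimates at no extra data cost

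*Protocol article*

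**What the plan says.** The section Data Analysis and Statistical Methods names one between-arm analysis, an unpaired two-sided t test that "will be used to examine the differences in mean change scores between the control and intervention groups regarding blood pressure"; weight, waist circumference and quality of life complete the list. It mentions no covariate.

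The section Preliminary Effectiveness and Outcomes sets aside health service utilization, which is collected only at week 8, and then states that "the other following outcomes will be measured at baseline and eight weeks postrandomization at the community center". The baseline value of every outcome in the t-test list is therefore already collected.

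The Phase II section randomises 60 participants 1:1. It lists these outcomes as secondary, under preliminary effectiveness; the primary outcomes concern implementation. A participant qualifies on blood pressure if they "had a systolic blood pressure between 140 to 159 mmHg or a diastolic blood pressure between 90 to 99 mmHg". The Implications section says that the results should help to launch a full randomised trial.

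**The concern.** A change-score analysis subtracts the whole baseline value, which amounts to assuming that the week-8 value rises by 1 unit for each unit of baseline. Blood pressure measured twice, eight weeks apart, normally has a slope below 1. If one arm then starts higher by chance, subtracting the full difference takes off too much, and the estimate moves in favour of the arm that started higher. Regression on baseline estimates the slope instead of fixing it. It removes this conditional error in expectation and usually gives a smaller standard error.

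What is at stake is limited: the precision of the effect estimates that this pilot hands to the design of the full trial. The analysis is a stated choice, not a gap that an analysis plan would fill, so it can be reviewed as written.

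**Working it through.** **1. The document's own figures.** The only effect and precision figures are those of the earlier classroom pilot (section Preliminary Work).
- Systolic: 3.8 mmHg, t = −1.58 on 55 df. The two-sided P is 0.120, matching the reported .12.
- Diastolic: 2.4 mmHg, t = −1.22 on 55 df. P is 0.228, matching .23.
- Analysed: 60 × 0.95 = 57, and 57 − 2 = 55 df. A 28/29 split is assumed.
- SE = difference / t: 3.8/1.58 = 2.41 and 2.4/1.22 = 1.97 mmHg.
- SD of change = SE / √(1/28 + 1/29) = SE / 0.265: 9.1 mmHg systolic and 7.4 mmHg diastolic.
- Systolic 95% half-width of the change-score analysis: 2.004 × 2.41 = 4.8 mmHg.

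**2. Textbook gain.** With equal SDs at both visits and correlation r, Var(ANCOVA)/Var(change score) = (1 + r)/2. With 57 analysed, estimating the slope multiplies the interval width by about √(1 + 1/53) × t(54)/t(55) = 1.0098. Adjustment therefore pays only if the variance ratio is below 1/1.0098² = 0.981.

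| r (assumed) | (1 + r)/2 | Half-width, mmHg | Narrower by |
|---|---|---|---|
| 0.4 | 0.70 | 4.07 | 16% |
| 0.6 | 0.80 | 4.35 | 10% |
| 0.8 | 0.90 | 4.62 | 4% |
| 0.98 | 0.99 | 4.84 | −0.5% |

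The last row stands for a very stable outcome such as weight.

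**3. Gain under the Phase II entry window.** The window narrows the spread of baseline blood pressure, so step 2 overstates the gain for blood pressure. The variance ratio is now s₁²(1 − ρ²) / (s₀² + s₁² − 2ρs₀s₁), where s₀, s₁ and ρ are the baseline SD, week-8 SD and correlation among those selected. These were found by simulation. Assumed, and not in the document: population SDs of 16 (systolic) and 10 (diastolic), correlation 0.6 between the two pressures, and means of 135/78 or 140/80. The table shows 140/80; at 135/78 the systolic gain is up to half a percentage point smaller and the diastolic gain is the same.

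| r | Systolic ratio | Systolic narrower by | Diastolic ratio | Diastolic narrower by |
|---|---|---|---|---|
| 0.4 | 0.886 | 4.9% | 0.761 | 11.9% |
| 0.6 | 0.930 | 2.6% | 0.845 | 7.2% |
| 0.8 | 0.967 | 0.7% | 0.925 | 2.9% |

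If everyone qualified through the systolic window, the systolic gain would run from 1.5% (r = 0.4) to −0.3% (r = 0.8).

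As a rough cross-check, the pilot's SD of change is nearest to the simulated systolic value at r = 0.8 (9.7 against 9.1) and to the diastolic value at r = 0.7 (7.6 against 7.4). There the gains are about 0.7% and 5%. This points to the lower part of each range, although the earlier pilot's entry criteria are not given.

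**4. Conditional error from chance imbalance.** The error is (1 − slope) × imbalance. In the simulation the slope equals r, 0.4 to 0.8, and selection leaves it unchanged. With the either/or window the systolic baseline SD is about 8.8 mmHg, so one SE of baseline imbalance is 8.8 × 0.265 = 2.3 mmHg. The change score then carries (1 − 0.8) × 2.3 = 0.5 to (1 − 0.4) × 2.3 = 1.4 mmHg. This is part of the t test's standard error, not an addition to it.

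**5. Validity of the planned test.** Simulated with no effect and a systolic window of 140–159, both analyses had means within 0.05 mmHg of zero and rejected in 4.6–5.1% of trials. Both arms fell alike through regression to the mean, and the fall cancelled in the comparison.

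**The case against.** The strongest reply is that nothing here is wrong. A t test on change scores is a legitimate analysis of a randomised trial, chance imbalance is already in its standard error, and the outcomes are secondary in a pilot. All of that stands. What remains is that the method is fixed in the text, the covariate is collected anyway, and the alternative costs almost nothing.

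Two stronger readings are tempting, and the document supports neither.

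- A reader might infer that enrolling people on raised blood pressure makes the change-score test biased. It does not. Regression to the mean affects both arms equally. A slope below 1 comes from imperfect correlation between visits, not from the entry window. By shrinking baseline variance, the window weakens the case for adjustment.
- A reader might infer a contradiction between planning a test and the statement "As a pilot study is not powered to be a hypothesis-testing trial, formal sample size calculations are not recommended". That sentence explains why there is no sample size calculation. It does not say that no test will be done, and nowhere does the article let P values decide efficacy or progression. Low power and multiple testing follow from the size and scope of a pilot, and adjustment would barely change either. How P values will be handled, and whether intervals accompany them, may be left to an analysis plan that is not shown.

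**Conclusion.** The point holds as a minor, essentially free improvement to the secondary outcomes. The planned test is valid and unbiased, but it fixes the baseline slope at 1 and so gives up some precision when the true slope is lower. The size depends on assumed correlations of 0.4–0.8 and assumed population SDs: intervals about 0–5% narrower for systolic and 3–12% narrower for diastolic blood pressure, and about 0.5% wider for an outcome with r near 0.98. The formula (1 + r)/2 should not be quoted for systolic pressure here, because it ignores the entry window. For waist circumference and SF-36v2 the document offers no basis for a figure.

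**What to change.** In Data Analysis and Statistical Methods, replace the t-test sentence with one to this effect: for systolic and diastolic blood pressure, weight, waist circumference and each SF-36v2 score reported, the week-8 value will be modelled linearly on arm and the baseline value of the same outcome (ANCOVA). The adjusted difference will be reported with its 95% confidence interval, as an estimate to inform the full trial.

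The cost is one or two sentences and one degree of freedom per model. No new data are needed, and the SPSS software already named can fit the model. The change should be made before outcome data are analysed.
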